## **8.0 STUDY PROCEDURE**

### **8.1 Referrals**

All people with a confirmed diagnosis of small cell lung cancer should be referred to the study as soon as possible after diagnosis to enable eligibility screening and baseline assessments to be conducted prior to Cycle 2 of chemotherapy or within three weeks from screening visit, if there is no planned chemotherapy. Therefore, potentially eligible participants will be identified by their own clinicians and referred to the study nurse after discussions with potential participants. The study nurse will ask the consultant in charge for permission to approach potentially eligible participants. This referral will be recorded within both the Data Collection Worksheet and eCRF and the participant's clinical file.

Attendance by the study nurse at key clinics will help to remind clinicians of the study and improve the likelihood of participant identification.

Local and central updates will be supplied to referring teams weekly and local prompts will be developed. These prompts will vary across sites according to the most appropriate form decided by the local teams and may include name-badge lanyard prompts, desk and consulting room office notice board prompts, or clinic posters.

### **8.2 Participant Informed consent process**

Obtaining consent for this study will be a process of information exchange between the study staff, the potential participant and any other person the potential participant believes should be included in the discussion. The participant information sheet will be used as a basis for the discussion, which will cover all procedures, benefits, burdens and side effects expected or possible during the study. The participant will be given opportunity (in time and physical capacity) to consider the study and formulate questions. Any questions will be addressed and answered fully. An actual time period is not specified as this will be determined in part by the participant condition. The study nurses will be trained to determine suitable time for discussion of the study against the participants' needs.

Prior to study commencement, during the site initiation visit, the study nurse, site coordinator and the investigator will be trained in consent procedures for this study, with the opportunity to role play scenarios and develop a consent script to ensure all information is fully covered.

***Anamorelin for anorexia, V1.6, 7 April 2022***

After checking with the clinical team to make sure the participant is feeling well enough to be seen, the Site Investigator or delegated staff member will introduce themselves to the participant and undertake the following:

- Explain the study and provide the participant information sheet. Give the participant time and privacy to read the information;
- Check to confirm participant is interested in participating;
- Obtain informed consent from the participant (please see below for details);

The consent form is completed by the Site Investigator or delegated staff member in accordance with the requirements of the HREC and site regulatory governance requirements. The form is signed and dated by the participant in their own handwriting.

If a potential participant is unable to read and if the legally acceptable representative is unable to read, an Impartial Witness should be present during the entire informed consent discussion. The Impartial Witness signs the Consent Form following:

- The Participant Information Sheet and Consent Form (and any other written material supplied) is read to the potential participant and / or their legally acceptable representative.
- The potential participant (or their legally acceptable representative) consents verbally to participation in the study.
- If able to do so, the potential participant (or their legally acceptable representative) signs and dates the Consent Form.

By signing the consent form, the Impartial Witness attests that the information in the Consent Form and any other written information was accurately explained to, and apparently understood by, the participant or the participant's legally acceptable representative, and that informed consent was freely given by the participant or the participant's legally acceptable representative. The witness can be any adult who observes the participant signing the consent form, and is able to say that the participant was signing of their own free will, but cannot be the researcher.

Where a witness is not required, but there is space on the consent form for 'Witness Signature' this section is struck through by the study staff with their initials and date, to indicate this section is not required as part of the informed consent process.

The completed consent form is copied (at the time of signing or on return to the study office) and filed:

- one copy is to be given to the participant;
- one copy is to be inserted into the medical file (with research sticker on file if required); and
- the original copy is to be filed in the study file.

### **8.3 Caregiver consent**

Any participant who has consented to join the study and who has been shown to be eligible will be asked to nominate their primary caregiver and for permission to approach them regarding the study/sub-study. The caregiver will then be approached and asked if they would be prepared to complete the caregiver unmet needs questionnaire, diary, and QoL assessments as per the study schedule, as well as participate in the sub-study schedules (detailed separately in the Sub-study Procedures Manual). If in agreement, they will be given the caregiver information sheet and asked to give informed consent for their participation. A primary caregiver should be 18 years and over and is defined as a spouse/relative, partner or friend of the patient who provides care for the person and not someone who has been employed to care for the person. Consent by the caregiver, or otherwise, will not have any effect on the continued participation of the eligible participant.

The completed caregiver consent form is copied (at the time of signing or on return to the study office) and filed:

- one copy is to be given to the caregiver;
- one copy is to be inserted into the medical file (with research sticker on file if required); and
- the original copy is to be filed in study file.

### **8.4 Screening for eligibility**

A Participant Master Index ([PMI] a document that tracks participant names, ID numbers, and progress through the study, developed and maintained at each site) will be kept of all potentially eligible participants including the reasons for non-entry.

Participants suitable for entry who are approached about the study and who have given informed consent will undergo a review of eligibility criteria and complete the eligibility screening:

- Some items will be obtained while in discussion with the potential participant.
- Specific items will require intervention or assessments for the purposes of research and can only be completed after informed consent to participate in the study has been obtained.
  - These items are to be left until it appears that the person is likely to be eligible; and
  - Informed consent is to be obtained prior to conducting the interventional assessments.
- Other items will be completed by referring to the person's clinical file or medical record.
- The plan of management will be checked with treating team (i.e. ensure no planned or likely change in management during the study period).

The completed eligibility screening will be reviewed by the Site Investigator and approval to proceed to randomisation will be obtained. If eligibility is confirmed proceed to baseline assessments and randomisation. A screening log will be kept of all potentially eligible participants including the reasons for non-entry. The screening data will be entered into the online database to enable the Project Officer at the ITCC to monitor eligibility of those enrolled in the study and cross reference with the randomisation process.

## **8.5 Re-screening**

In some cases it is possible that potential participants will need to be re-screened, for example:

- If a person consents to participate, meets the eligibility criteria but there is a delay in starting due to a change in situation (family issues, individual request for attending private matter, etc.);
- If the person previously failed eligibility due to an acute event that has now resolved; or
- Medications have now stabilised.

In these situations, if randomisation has not occurred:

- A new eligibility form is used;
- A new ID number is assigned to the participant;
- The participant is flagged as having been re-screened on both the eCRF and the PMI;
- The eligibility form is completed as if being fully screened, data is not copied from one form to the next, but completed using the current clinical situation as documented within the patient clinical notes.

It is not appropriate to re-screen a person if they have previously failed to meet the eligibility criteria and there have been no further changes or treatments that would now indicate that the patient may be suitable.

## **8.6 Procedure to request randomisation**

The third party pharmacy will be contacted whenever a person is undergoing the screening process to warn them of a potential trial candidate. This will be followed up by a confirmatory call as soon as the person's eligibility has been confirmed.

The randomisation request will take the form of the prescription of the study medications. Upon receipt of the prescription, the pharmacist at the third party pharmacy will then prepare the study medication according to the allocation received from the ITCC Central Randomisation Service. The allocation email will be filed in the pharmacy study folder.

The pharmacist will identify the study medications for the participant according to the allocation prescription in the supplied schedule and label the blinded study medication kits providing the details as described in section 4.4.

## **8.7 Prescription of study drugs**

All prescriptions for the use of investigational products for clinical trials must be:

- Completed by a person authorised to do so:
  - the Principal site investigator;
  - sub/co investigators;
  - those medically authorised and delegated on the study to prescribe the specific product under investigation.
- Completed on a hospital prescription form and detail full description of the:
  - participant details;
  - study protocol number;
  - stratification details for disease extent and FAACT score
  - drug (this will be anamorelin or placebo);

- dose (this will specify the dose level/s);
- frequency;
- route.

In this study the prescription will therefore read:

*ID No. 044/21 'Anamorelin 100mg / Placebo: swallow one capsule whole each morning at least one hour before food. Please supply 1 study medication kit.'*

## **8.8 Treatment commencement**

The study medication will commence on the same day of delivery if participant has not eaten first meal of the day (start Day 1). If a fasting state is not possible on Day 1, participants will start study drug on the next possible day but **no later** than one day prior to planned day 1 of Cycle 2 of chemotherapy. Dosing is thereafter to continue daily, 1 hour prior to the first meal of the day.

## **8.9 Assessment visits**

Participants will visit the study centre at baseline, Weeks 4, 8 and 12 (and 18 and 24 for those in the extension phase). During the visit, the study nurse will take the measures and assessments as outlined in the table of study measures (Table 6-1) and record the visit in the Data Collection Worksheet for that time point. This visit will also be recorded within the participant clinical file. Participants will be offered remuneration to cover parking or taxi fares to attend the study clinical visits, if required.

## **8.10 End of treatment assessments**

Collection of end of treatment data will occur following the last dose of the study intervention (or when treatment is ceased, if earlier cessation occurs). During the visit, the study nurse will take the Week 12 measures and assessments as outlined in Table 6-1 of study measures and record the visit in the Data Collection Worksheet and eCRF. This visit will also be recorded within the participant clinical file, along with any instructions or changes regarding ongoing management.

If early cessation due to an AE, all associated documents will be completed (Serious Adverse Event (SAE) report, AE assessment score etc.).

An AE with a grade of 3 (that has not responded to symptomatic treatment instituted by the treating physician according to local protocols) or 4 will activate treatment cessation and an AE report will need to be completed and submitted. Please refer to Section 10 for further information about AE and SAE reports.

### **8.11 Withdrawal assessments**

If participants are to be withdrawn, a 'Withdrawal Data Collection Worksheet' will be completed by the study nurse on instruction from the investigator. The early termination/withdrawal assessments outlined in Table 6-1 of study measures will be completed [as soon as practicable/within 7 days of withdrawal] and reason for withdrawal will be recorded.

### **8.12 Follow-up phase assessments**

All participants will be followed by their clinician for continuing care, irrespective of the point at which they exit the study. For all study participants, regardless of above choices, study outcomes and collection of data for economic evaluation will occur until the end of 12 weeks after randomisation, unless consent is withdrawn.

Participants will be followed up by telephone weekly irrespective of their place of care for 4 weeks or death or withdrawal of consent, whichever is the shorter period. The date of death will be collected from medical records even if this occurs after the 4-week follow-up. The contact data will be recorded in the follow-up Data Collection Worksheets and eCRF, and will provide data on compliance with cancer treatment, side effects and long term clinical and economic outcomes. The nurse will use the telephone number recorded in the discharge details and will clearly identify themselves. The nurse will ask for information as outlined in the data collection worksheets and will record this while talking with the participant. A medication list will be updated at each contact to record actual prescribed and taken medications since the preceding visit.

Date of death will be recorded for all participants collected from existing medical records.

### **8.13 Extension phase criteria**

At the end of the 12 weeks, participants are invited to enrol in an extension phase where they will continue to receive blinded intervention medication for another 12 weeks. The optional extension (for Weeks 13-24) is entirely based on participant's preference. During the extension phase frequency of AEs, quality of life, medication usage and compliance will be measured up to death or 28 days after ceasing study medication (whichever is the shorter period). These data will be collected via a weekly telephone call to the participant if they have been discharged home and recorded in the follow-up Data Collection Worksheet and eCRF as outlined above. The extension assessments outlined in Table 6-1 of study measures will also be completed.

### **8.14 Sub-study**

The sub-study is detailed in a separate document – the Sub-study Procedures Manual.

## **9.0 STUDY ADMINISTRATION AND MONITORING**

### **9.1 Reporting of adverse events**

All AEs will be reported via an online reporting system to enable study-wide reporting. The ITCC has an SOP for AE reporting that will operate at all study sites (SOP 5.17, Adverse Event Reporting). In addition, there will be specific events and reporting mechanisms required due to the nature of the study drug. This is described below. SAEs will be reported to ITCC, Human Research Ethics Committees (HREC) as per their standard operating procedures; and to the Medical Monitor within 24 hours of knowledge of the event.

#### ***9.1.1 The Trial Management Committee***

A Trial Management Committee (TMC) will be created for this study. Each meeting of the TMC will receive from the ITCC a summary report of the AEs reported by the investigators, along with data and recruitment updates. Each summary report will be generated from the on-line entry of AE reports by participating sites into REDCap. This summary report will be reviewed for reporting compliance, trends in events, and outstanding events that require specific attention. Minutes will be taken at all Trial Management Committee discussions, with action items detailed, and reviewed at the subsequent meeting. The TMC will not have access to unblinded reports of AEs.

#### ***9.1.2 Human Research Ethics Committees***

AEs and SAEs are to be reported to site HRECs as per each HREC reporting guidelines and where appropriate the Medical Monitor in the format and timeframe stipulated by each individual committee.

#### ***9.1.3 Medical Monitor***

A Medical Monitor (MM) will be assigned to review and evaluate information relevant to the safety of the investigational product used. The MM has the responsibility to review and evaluate information relevant to the product safety throughout the implementation of the protocol at all participating sites.

The MM will be responsible for providing safety oversight and reviewing the protocol (e.g., study halting rules) and information about the study product as it becomes available, such as the reportable safety events (SAE's).

***Anamorelin for anorexia, V1.6, 7 April 2022***

The MM, in consultation with the protocol investigator team and the Sponsor will provide safety review during the execution of the clinical trial. This oversight includes reviewing safety information and providing applicable recommendations. The MM will provide recommendations, as appropriate, to members of the study and investigator team. This data and safety review facilitates early detection of safety signals and maximizes the chances for continued appropriateness of the research and protection of human participants.

Based on a synthesis of this information, the MM will provide appropriate recommendations to the Sponsor, participating recruiting sites and approving HRECS.

#### **9.1.4 Adverse events**

AEs are defined as any untoward or unexpected occurrence in a patient or clinical investigation participant where the occurrence does not necessarily have a causal relationship with the study intervention.

There are circumstances where AEs will not be reported, however their occurrence will still be recorded in the data collection worksheets and eCRF. Examples are:

- an expected side effect from a study intervention, such as constipation unless the side effect required additional treatment or assessment;
- signs or symptoms associated with the disease or disorder under study, unless they are more severe than expected;
- social admission to hospital.

#### **9.1.5 Serious adverse events**

SAEs are any untoward medical occurrence that: meets one or more of the following criteria/outcomes:

- death;
- life-threatening (i.e. at immediate risk of death);
- in-patient hospitalisation or prolongation of existing hospitalisation;
- persistent or significant disability/incapacity;
- congenital anomaly or birth defect;
- other medically relevant condition judged as serious.

- “Life threatening” means that the participant was at immediate risk of death from the event as it occurred. It does not include an event that, had it occurred in a more serious form, might have caused death.
- “Requires inpatient hospitalisation” is defined as hospital admission for treatment of the AE. Hospital admission for scheduled elective surgery would not be an SAE.
- “Other medically relevant condition judged as serious” is where medical and scientific judgment should be exercised in deciding whether expedited reporting is appropriate in other situations, such as important medical events that may not be immediately life-threatening or result in death or hospitalisation but may jeopardise the participant or may require intervention to prevent one of the other outcomes listed in the definition above. These should also usually be considered serious. Examples of such events are intensive treatment in an emergency room or at home for allergic bronchospasm; blood dyscrasias or convulsions that do not result in hospitalisation; or development of drug dependency or drug abuse. A diagnosis of a new cancer during the course of the treatment should be considered as medically important.

Progression of a participant’s underlying condition leading to one of the above should always be reported as a serious (but expected) AE, which is unrelated to protocol treatment, or caused by failure of the anticipated therapeutic effect of the study drugs/intervention.

The expected study population have an underlying disease that is expected to significantly shorten life expectancy, they are already termed palliative and are expected to die within a short period of time. In this study, a number of SAEs may be anticipated, but these are unlikely to be attributable to the study intervention.

The conditions recognised as being excluded from the usual SAE reporting timeframes (but are still to be recorded as SAEs) are as follows:

- Where participants are admitted as a planned admission due to respite, family or social issues, or for pre-planned treatment.
- Where participants are admitted (or admission is prolonged) due to a documented expected deterioration in their condition due to the underlying disease process, or where the admission is prolonged for this reason.
- Where participants die due to a well-documented decline in their condition due to the underlying disease process.

In all other cases, SAEs will be reported by the study site, to the ITCC by completing a Serious Adverse Event Report Form and sending it to the ITCC within 24 hours of first knowledge of the event per ITCC SOP 5.17 Adverse Event Reporting. SAEs will be reported according to the requirements of the hospital HREC and/or local Research Governance Office (RGO) and also reported within 24 hours to the MM. A subset of all deaths that occur during the study including during follow-up will be randomly selected for evaluation by the MM.

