#### **9.1.9      *National Cancer Institute, Common Terminology Criteria for Adverse Events. (NCI CTC AE).V5.0***

These criteria have been used to determine AEs likely to occur during the study period and will be used to determine AE reporting and study progress. Criteria specific to the expected events known to be associated with anamorelin have been listed. This is administered by study staff.

Symptoms will be identified during each visit using criteria established by the National Cancer Institute, and will be graded accordingly. Specifically, for this study, the symptoms of interest will be:

- Symptomatic hyperglycaemia (dizziness, cold sweat, loss of consciousness, abdominal pain, shortness of breath, confusion), constipation, nausea, vomiting.
- Blood glucose increased (investigation)
- Symptoms of cardiac dysfunction (PR prolongation and increased QT interval measured on ECG), blurred vision, breathlessness, chest pain, syncope, palpitations
- Headache
- Peripheral oedema

A grade of 3 (that has not responded to symptomatic treatment instituted by the treating physician according to local protocols) or 4 will activate cessation of study intervention and an SAE report. All AEs will be collated by the project officer and reported to the executive committee on a monthly basis. AE rates will form part of the Key Performance Indicators for the study and will be reported on a regular basis to the Trial Steering Committee and the ethical review boards of the participating sites.

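### Section 9.1.5 limits serious hospitalisation to admissions that treat an AE, then has planned admissions recorded as SAEs; 8.10 and 9.1.9 name different reports for the same grade trigger

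*Supplement*

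**What the plan says.** **Planned admissions.** Section 9.1.5 defines an SAE as an untoward medical occurrence that meets one of the usual outcome criteria, including inpatient hospitalisation. It explains that criterion narrowly: it "is defined as hospital admission for treatment of the AE. Hospital admission for scheduled elective surgery would not be an SAE". Further down, the same section waives the usual reporting clock for three situations: "The conditions recognised as being excluded from the usual SAE reporting timeframes (but are still to be recorded as SAEs) are as follows". The first situation reads "Where participants are admitted as a planned admission due to respite, family or social issues, or for pre-planned treatment". The other two are admission for, and death from, documented decline of the underlying disease.

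Section 9.1.4 lists occurrences that are not reported as AEs but are still entered in the worksheets and eCRF. One example is "social admission to hospital".

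**Grade trigger.** Sections 8.10 and 9.1.9 use the same trigger: grade 3 that symptomatic treatment has not controlled, or grade 4. In 9.1.9, after the list of symptoms of interest, such a grade "or 4 will activate cessation of study intervention and an SAE report". In 8.10 it "or 4 will activate treatment cessation and an AE report will need to be completed and submitted". The paragraph just before that in 8.10 also names an SAE report among the documents to complete when treatment stops early because of an AE.

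**Use of the data.** Safety is the first item in the primary objective (2.2.1). Section 10.4 summarises all safety data descriptively. No SAE-rate endpoint, threshold or test is named.

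**The concern.** A planned admission for treatment or respite is not untoward and need not treat any AE. Under the definition in 9.1.5 it is not an SAE; under the list in the same section it is recorded as one. Two sites could classify the same admission differently, and both would be following the protocol.

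The same holds for a grade 4 symptom of interest that meets no seriousness criterion. One section calls for an SAE report and another for an AE report, while severity (9.1.6) and seriousness (9.1.5) are defined separately.

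Safety feeds the phase III decision through descriptive tables alone, with about 25 participants per arm. What counts as an SAE therefore has to be settled before those tables are read. AE rates are also a key performance indicator for oversight (9.1.9).

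**Working it through.** The plan states no figure on this point, so there is nothing to reproduce. The check is a comparison of texts, followed by an illustration of the consequence.

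**1. Planned or social admission with no adverse event**

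| Place | Status it gives |
|---|---|
| 9.1.5, hospitalisation criterion | Not serious: the criterion "is defined as hospital admission for treatment of the AE" |
| 9.1.5, elective surgery | Not serious: "Hospital admission for scheduled elective surgery would not be an SAE" |
| 9.1.5, first item of the timeframe list | Recorded as an SAE, reporting timeframe waived |
| 9.1.4 | Social admission: recorded, not reported as an AE |

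Sections 9.1.4 and 9.1.5 agree that such an admission is recorded without the usual reporting. They differ on the label under which it is recorded. The conflict inside 9.1.5 is direct. Elective surgery and pre-planned treatment overlap without being identical terms, but the treatment-of-the-AE rule covers both.

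The other two items on the list fit the label. 9.1.5 says that disease progression leading to a serious outcome is always a serious, expected event. Only the first item is out of place.

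**2. Grade 3 not controlled by treatment, or grade 4**

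| Place | Report required |
|---|---|
| 9.1.9 | SAE report |
| 8.10, the sentence on grades | AE report |
| 8.10, the preceding paragraph | SAE report listed for early cessation due to an AE |
| 9.1.5 | Neither grade nor cessation is a seriousness criterion |

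8.10 sends the reader to Section 10 for AE and SAE reports. Section 10 is Statistics; AE reporting is in 9.1. The cross-reference does not settle the matter.

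**3. Effect on the summary (illustration; all rates are assumptions)**

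Let p be the proportion of participants with true serious harm. Let q be the proportion with a planned admission recorded as an SAE, equal in both arms and independent of harm. The proportion with at least one recorded SAE is

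1 - (1 - p)(1 - q),

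so the between-arm difference is (1 - q) times the true difference. With p = 20% (control) and 40% (active):

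| q | Control | Active | Difference | Risk ratio | Control 'SAE' participants with no serious harm |
|---|---|---|---|---|---|
| 0 | 20% | 40% | 20 points | 2.00 | 0% |
| 10% | 28% | 46% | 18 points | 1.64 | 29% |
| 30% | 44% | 58% | 14 points | 1.32 | 55% |
| 50% | 60% | 70% | 10 points | 1.17 | 67% |

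Example at q = 30%: control 1 - 0.8 x 0.7 = 0.44; active 1 - 0.6 x 0.7 = 0.58; share without harm (0.44 - 0.20)/0.44 = 0.55.

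With p = 10% and 30%, the difference shrinks by the same factor and the risk ratio falls from 3.0 to 1.38 at q = 30%.

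If SAE records are counted instead of participants, adding the same mean number to each arm leaves the absolute difference unchanged but still pulls the ratio towards 1.

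**The case against.** The case for leaving the text largely alone has several parts.

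- **Recording is not reporting.** 9.1.4 and 9.1.5 both keep these admissions out of the usual reporting while recording them. This stands, and it narrows the disagreement between the two sections to the label. It does not help within 9.1.5, which asks for recording as SAEs.
- **8.10 can be read with 9.1.9.** Its preceding paragraph already lists an SAE report when treatment stops for an AE, and these grades stop treatment. A reporting route also need not redefine seriousness, and 9.1.5 allows medical judgement. This stands in part: the grade conflict is the smaller of the two. The wording still differs on one trigger.
- **Unseen material may govern.** AE handling is assigned to SOP 5.17, and the diagram in 9.1.10 is not shown. Either might settle the classification, so one cannot say that sites have no rule. The protocol text would still conflict.

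Three stronger readings are tempting, and the documents support none of them.

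- *The SAE rate fails to measure serious harm.* The core criteria in 9.1.5 are conventional and true SAEs are still captured. No SAE-rate endpoint is named, and safety also draws on examination, ECG, laboratory tests, graded symptoms and survival.
- *The arm that completes more planned chemotherapy is penalised.* This could happen for treatment admissions. Respite and social admissions sit in the same item and could be commoner in the arm doing worse. The direction is unknown.
- *Dozens of spurious SAEs will appear.* Assuming that 10% to 30% of 50 participants have 3 to 4 planned admissions each gives 50 x 0.10 x 3 = 15 to 50 x 0.30 x 4 = 60 records. Neither input is in the protocol; 11.3.4 says only that participants may be inpatients or outpatients. Repeat admissions also add nothing if participants, not events, are counted.

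**Conclusion.** The inconsistency inside 9.1.5 is real in the current text. Followed as written, it places admissions that involve no adverse event in the SAE data, and it should be corrected. The differing report wording in 8.10 and 9.1.9 is a second, lesser inconsistency.

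The consequence is a descriptive SAE summary that does not cleanly measure serious harm. With q equal in both arms and independent of harm, a difference in SAE proportions is diluted by (1 - q): little at q = 10%, by half at q = 50%. If q is near zero the numerical effect disappears, though the texts still conflict. If q differs between arms, the error can go either way. The protocol supplies no value of q, so size and direction remain open.

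The rule on stopping study drug is not judged here.

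**What to change.** - **9.1.5:** remove planned admissions from the recorded-as-SAE list. State that a planned admission with no underlying AE is logged separately and is neither recorded nor tabulated as an SAE. Leave the two disease-decline items where they are.
- **9.1.4:** use the same status for social admissions and refer to 9.1.5.
- **8.10 and 9.1.9:** reconcile the report required for the shared grade trigger, and correct the reference in 8.10 from Section 10 to Section 9.1.
- **10.4:** state that the SAE table holds only events meeting a 9.1.5 criterion, whatever reporting route the grade trigger uses, and whether it counts participants, events or both.
- Check SOP 5.17, the diagram in 9.1.10 and the eCRF field for the same wording.

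The cost is a text amendment and a possible change to one eCRF field. No new data are needed. Nothing on harm is lost, because unplanned hospitalisation is already a separate endpoint (5.2.1) and admissions that treat an AE remain SAEs. No large saving in expedited forms should be expected, since the listed admissions are already outside the 24-hour route.
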